### Allocation

Groups of teams or a team were randomized in a 1–1 allocation between the intervention and control groups. The groups were balanced across type (primary care internal medicine, family medicine, and pediatrics) and panel size (large vs. other). A computer algorithm accessed by the study statistician randomized the groups using dynamic allocation [17]. Blinding did not occur.

Concerns about contamination did not allow for randomization at the care team level as staff within a care team could overlap with other sites and other care teams within a site. After recruitment had completed, the study team statistician assessed the staff overlap and grouped the teams based on this to ensure that each unit of randomization was unique.

### Methods for data collection

Self-reported responses from staff within the enrolled care teams attending the huddles were collected at baseline and 6 months post enrollment. The intervention group completed the survey at 100 days as well. The survey is the same for each time point with the exception of the 6-month survey, which also had questions to assess burnout [18]. The surveys were sent via email, with up to three reminders for non-responders.

For the quality metrics, the data were from aggregated medical records for all patients assigned to the care team. The time frame for collection was from 6 months prior to the start of the study to 12 months post (6 months after the end of the intervention period). The metrics are described in Section “Outcomes”.

The following measures were collected pre-intervention, after 100 days (intervention only), and after 180 days (Additional file 3). The scales collected include team cohesion, psychological safety, and team autonomy. Team cohesion captures the extent to which members of the care team stick together in terms of helping each other and defending each other from criticism. It was measured using a four-item scale adapted from Lewis [19]. Psychological safety measures the extent to which care team members can freely express their opinions without negative repercussions. It is defined as “a shared belief that the team is safe for interpersonal risk taking.” Psychological safety is measured using a six-item scale developed by Edmondson [20]. Team autonomy measures the degree of involvement of the care team members in determining huddle goals, performance evaluation, and task assignment. A five-item scale adapted from Thompson was used to measure autonomy [21]. For staff demographics, we collected gender and provider role.

### Data management

Survey data were collected by the Survey Research Center, which is an institutional resource for conducting mail, web, and telephone surveys. The Survey Research Center works closely with Mayo Clinic’s IRB to ensure compliance with legal requirements and Mayo Clinic’s policies for surveys. All Survey Research Center staff receive IRB and HIPAA training, testing, and supervision to ensure the information dealt with is treated confidentially and consistent with Mayo policy. Data captured from the assigned patients at the care team level will be stored within the Mayo Clinic system, which is password protected and backed up every night. Press Ganey ® patient satisfaction surveys are administered via mail by Mayo Clinic. Mayo Clinic statistical study team members have access to study data.

### Statistical methods

All teams will be analyzed in the arm to which they were assigned using techniques appropriate for pragmatic cluster randomized trials. Baseline characteristics will be summarized at the site and care team levels within each trial arm, to provide counts and frequencies for categorical variables and means with standard deviations and ranges for continuous variables. We will test the null hypothesis of no difference between arms in baseline characteristics using *t*-tests and chi-square tests adjusted for clustering by care team.

To account for the effects of care team clustering, we will use hierarchical generalized linear models with random main effects specified at the care team level. Such models are appropriate for analyzing cluster randomized trials and will allow us to account for any imbalances in care team characteristics across study arms. For measures collected from the team members, the outcome of interest will be the 6-month post-baseline responses, adjusting for baseline responses. If there are differences in baseline characteristics between the two study groups, these will be accounted for using hierarchical generalized logistic or linear regression models that include an indicator for study arm.

For outcomes collected at the care team level (patient satisfaction and quality measurements), the percentage of patients who gave the top score for satisfaction and the percentage of patients who met the quality criteria will be compared between arms without accounting for clustering effects, as the data are not available at the individual level.

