**Methods/design:**

We will conduct a care-team-level cluster randomized trial within primary care practices in two Midwestern states. The intervention will comprise a 1-day training retreat for leaders of primary care teams, biweekly sessions between huddle optimization coaches and members of the primary care teams, as well as coaching site visits at 30 and 100 days post intervention. This behavioral intervention will be compared to standard care, in which care teams have huddles without any support or training. Surveys of primary care team members will be administered at baseline (prior to training), 100 days (for the intervention arm only), and 180 days to assess team dynamics. The primary outcome of this trial will be team morale. Secondary outcomes will assess the impact of this intervention on clinician burnout, patient satisfaction, and quality of care.

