### Outcomes

The primary outcome for the trial is a previously tested and validated team measurement score that consists of 31 questions, asking the respondent to answer “agree” or “disagree” on a four point scale that is converted to a 100 point score per methods referenced in Stock et al. [15]. The team measurement score focuses on four elements of team behavior: communication, roles and goals, cohesion, and team primacy. Responses from each team member will be used to generate an overall score for the team.

Secondary aims include patient satisfaction assessed through Press Ganey ® Medical Practice surveys. These surveys are implemented routinely within the health-care system. After a patient has had an appointment, if they are randomly selected, the survey is sent to them within 30 days for completion. A random sample of each team’s assigned patients that had a recent appointment were surveyed by Press Ganey® every quarter and reported at the site, care team, and provider levels. Patients’ responses are de-identified so that we know who provided the care but not to whom. We receive the percentage of patients who rated their provider with a top score for a given quarter. We monitor the quality outcomes in chronic disease management and prevention to ensure safety and an adequate quality of care are provided in both the control and intervention arms. Quality metrics at the care team level are assessed monthly for diabetes, depression, asthma, hypertension, and vascular issues. The metrics are calculated as the number of patients who met the quality criteria divided by the number of patients who are assigned to the care team who qualify for the assessment. The criteria for each metric are set by Minnesota Community Measures [16].

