### Trial status

In total, 30 care teams responded to the email invitation to participate. The 30 care teams consisted of 23 unique randomizing units due to staff overlap. Post-randomization prior to the baseline surveys being sent out, one unit that had one care team and another two care teams withdrew from participation. Excluding the care team that withdrew, 11 units were randomized to the intervention arm (13 care teams) and 11 to usual care (16 care teams). The retreat took place on 13 April 2017. Data collection is still ongoing.

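### The survey models cluster on the care team, although the randomised unit was a team or a group of teams sharing staff; if outcomes correlate within units, the primary test is modestly anti-conservative

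*Protocol article*

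**What the plan says.** Statistical methods gives one clustering level for measures collected from team members: "we will use hierarchical generalized linear models with random main effects specified at the care team level". It describes such models as suitable for cluster randomised trials. The tests of baseline characteristics are adjusted for clustering by care team as well.

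Allocation describes a different unit: "Groups of teams or a team were randomized". The reason given is "Concerns about contamination did not allow for randomization at the care team level as staff within a care team could overlap with other sites"; overlap between teams at one site is named too. After recruitment the statistician assessed the overlap and "grouped the teams based on this to ensure that each unit of randomization was unique".

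Trial status gives the counts: "The 30 care teams consisted of 23 unique randomizing units due to staff overlap". After withdrawal it reports 11 units with 13 care teams in the intervention arm and 11 units with 16 care teams in usual care.

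The abstract nevertheless says "We will conduct a care-team-level cluster randomized trial within primary care practices in two Midwestern states". Nowhere does the article mention a random effect, a robust variance or degrees of freedom for the randomised unit.

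**The concern.** In a cluster randomised trial the analysis has to respect the level at which allocation was made. Here the modelled cluster lies below that level wherever a unit holds more than one team. Such teams received the same allocation and were merged because they share staff, so their outcomes can be expected to correlate. A model whose only cluster term is the care team treats them as independent and counts 29 clusters where 22 were randomised. A person who works in two teams also does not fit a strictly nested team effect.

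At stake are the confidence interval and the test for the primary outcome. With correlation between teams in a unit, the interval is too narrow and the nominal 5% test rejects too often.

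**Working it through.** **1. The plan's own power figure.** Inputs from Sample size: k = 10 clusters per arm, m = 10 people per cluster, ICC 0.05, difference 0.5 SD, two-sided alpha 0.05.
- Design effect: 1 + (m − 1) × ICC = 1 + 9 × 0.05 = 1.45.
- Effective number per arm: 100 / 1.45 = 69.0.
- Noncentrality: 0.5 / √(2 / 69.0) = 2.94.
- Power: 79.3% (t, 18 df) or 83.6% (normal). The stated 80% is reproduced.

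The companion figure (m = 3, 1 SD, 90%) comes out at 93.7% (t, 18 df), so it is met as a minimum.

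**2. How many units and teams are affected.**
- 30 teams − 23 units = 7 extra teams. At most 7 units hold more than one team, so at least 16 are single teams.
- After withdrawal, the intervention arm has 13 − 11 = 2 extra teams. Its multi-team units hold 3 teams (one unit of three) or 4 teams (two pairs).
- Usual care has 16 − 11 = 5 extra teams. Its multi-team units hold between 6 teams (one unit of six) and 10 teams (five pairs).
- In total 9 to 14 of the 29 teams (31–48%) share a unit with another team.

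**3. Standard error.** The layout of teams over units and the share of the ICC that lies between units are not in the article, so both are varied. Equal team sizes are assumed and total variance is set to 1. In an arm with T teams and n_j teams in unit j, the variance of the mean of team means is

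true: σ²_unit × Σn_j² / T² + σ²_team / T + σ²_error / (mT)

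assumed by the model: (σ²_unit + σ²_team) / T + σ²_error / (mT)

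With ICC 0.05 and m = 10, σ²_error / m = 0.095, and 1/13 + 1/16 = 0.1394. The model's variance for the arm difference is (0.05 + 0.095) × 0.1394 = 0.0202.
- *Extra teams as pairs:* Σn_j² / T² summed over arms is 17/169 + 26/256 = 0.2022. With the whole ICC between units, the true variance is 0.05 × 0.2022 + 0.095 × 0.1394 = 0.0234. The SE ratio is √(0.02335 / 0.02022) = 1.075.
- *Extra teams in one unit per arm:* 19/169 + 46/256 = 0.2921. The true variance is 0.0279 and the SE ratio is 1.174.
- With half the ICC between units, the ratios are 1.038 and 1.090.

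These two layouts give the smallest and largest Σn_j² that the counts allow.

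**4. Type I error.** Simulated under the null with 60,000 runs per scenario, using REML with a care-team random effect only and t on 27 df (29 teams − 2). ICC is 0.05.

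| Share of ICC between units | m = 10, pairs | m = 10, one large unit per arm | m = 3, both layouts |
|---|---|---|---|
| 0 | 4.7% | 4.9% | 4.1–4.2% |
| 50% | 5.6% | 7.0% | 4.5–5.0% |
| 100% | 6.6% | 9.2% | 4.6–5.7% |

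The SE ratios give a hand check. For pairs at 100%, the critical value 2.052 / 1.075 = 1.909, with a two-sided tail of 6.7% on 27 df. For one large unit per arm, 2.052 / 1.174 = 1.748, with a tail of 9.2%.

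At an assumed ICC of 0.20, m = 10 and shares of 50–100%, the error is 7.0–14.8%. A t test on unit means (20 df) stays at 4.8–5.2% throughout.

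**5. Power after the change.** With 11 units per arm, 10 staff per unit and ICC 0.05 at the unit, the effective number is 110 / 1.45 = 75.9 per arm and the noncentrality is 3.08. Power for 0.5 SD is 83.4% (t, 20 df).

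**The case against.** The best defence is that the mismatch touches few units and may cost little. In at least 16 of 23 units, team and unit are the same thing. Inflation needs correlation between teams beyond that within a team, and the article gives no figure for it. With none, or with the minimum of three respondents per cluster and the planned ICC, the error stays near 5%. Adjustment for baseline responses may also reduce between-unit variance. All of this stands, and it limits the size of the problem. It does not make the care team the right level.

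The count of 29 teams is also uncertain. Trial status mentions two further care teams that withdrew, and it is unclear whether 13 and 16 already exclude them. If 27 teams remain in 22 units, simulation of five assumed layouts (ICC 0.05, m = 10, t on 25 df) gives 5.2–6.4% at a 50% share and 5.8–7.5% at 100%. The mismatch remains.

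It could be said that the unshown analysis plan will settle the level. But the article does not leave it open: it names the care team, and an analysis plan that followed it would inherit the error. Nor can care team be read loosely as randomised unit, since Allocation and Trial status separate the two and count them differently.

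Some stronger readings are tempting but not supported:
- That all 23 units are groups of teams, or that type I error certainly exceeds 5%. The first contradicts the counts, and the second depends on an unquantified variance.
- That the error is generally above 10%. This needs an ICC well above the planned 0.05, or a normal reference, which adds a separate small-sample problem (5.8–5.9% at m = 10 with no unit effect at all). The article specifies neither t nor z.
- That the model cannot be fitted because "Responses from each team member will be used to generate an overall score for the team". Statistical methods takes team members' 6-month responses as the outcome, so individual data appear to be modelled.
- That staff in several teams are counted twice. The article does not say so.

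**Conclusion.** The analysis level is wrong as written. The survey models and the baseline tests cluster on the care team, while allocation was to teams or groups of teams. The direction of the error follows from the design, but its size is conditional and modest. At the planned ICC with 10 staff per team and a t reference, type I error is roughly 5.5–7% if half the ICC lies between units and 6.5–9% if all does. The true standard error is then 4–9% or 8–17% above the one reported. Larger ICCs give more. These figures rest on assumed layouts, assumed variance shares and equal team sizes, and the simulation included no baseline covariate. Because the point governs the primary test and is cheap to correct, it should be corrected.

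**What to change.** - In Statistical methods, specify a random intercept for the randomised unit, with care team nested within it if estimable.
- Base the small-sample degrees of freedom for the arm effect on the 22 randomised units.
- Use the same level for the clustered baseline tests.
- In the abstract, describe the trial as randomising care teams or groups of care teams, since Allocation says "Concerns about contamination did not allow for randomization at the care team level".
- In Trial status, state whether the team counts exclude the two further withdrawn teams.

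The cost is a change of wording and one model term. No new data are needed, and Trial status reports that collection was still under way. Intervals become slightly wider. The power of about 83% for 0.5 SD assumes 11 equal units per arm with 10 staff each.

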### Sample size

Assuming 10 clusters per arm with an intra-cluster correlation of 0.05, with a minimum of three participants per cluster, we would be powered at 90% to detect a 1 standard deviation difference between continuous outcomes. If the cluster size is 10 individuals, then we would be powered at 80% to detect a half standard deviation difference between two continuous outcomes. All calculations are based on a two-sided test with an alpha of 0.05. To ensure there was adequate support for the retreat and that the coaches can support the teams, a maximum of 15 care teams can be randomized into the intervention arm.

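### Baseline characteristics are adjusted for only if the arms differ, so practice type and panel size, balanced at allocation, would almost never enter the model

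*Protocol article*

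**What the plan says.** Under Statistical methods, the protocol article plans significance tests of the baseline table: "We will test the null hypothesis of no difference between arms in baseline characteristics". It then makes adjustment depend on what is found: "If there are differences in baseline characteristics between the two study groups, these will be accounted for" in the hierarchical regression models that carry the arm indicator.

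One covariate is unconditional. For measures collected from team members, "the outcome of interest will be the 6-month post-baseline responses, adjusting for baseline responses".

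Under Allocation, a computer algorithm "randomized the groups using dynamic allocation", and the factors used are named: "The groups were balanced across type (primary care internal medicine, family medicine, and pediatrics) and panel size (large vs. other"). Neither factor is named as a model term under Statistical methods.

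Under Methods for data collection, the surveys are the same at each time point "with the exception of the 6-month survey, which also had questions to assess burnout". Burnout therefore has no baseline response.

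**The concern.** Allocation and analysis work against each other. Allocation removes differences in practice type and panel size, and the analysis rule looks for differences before it adjusts. The two factors thought important enough to balance are the two that the rule is least likely to pick up.

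When a prognostic factor is balanced by design, the arm contrast really does vary less between trials. A model without the factor still leaves its variance in the residual, so the reported standard error is larger than the true one. The test then rejects too seldom and power is given away, in a trial with 22 randomized units.

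A second, smaller matter is that characteristics not balanced by design enter or stay out by chance, so the final model is not fixed in advance.

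**Working it through.** **Inputs from the protocol article.** Sample size: 10 clusters per arm, intra-cluster correlation (ICC) 0.05, cluster size m of 3 or 10, two-sided alpha 0.05. Trial status: 11 units per arm. **Assumed, because not given:** the share of cluster-mean variance that type and panel size explain.

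**1. The plan's own power.** The design effect is 1 + (m − 1) × ICC, and the standard error in SD units is √(2 × design effect / (clusters per arm × m)).
- m = 10: design effect 1 + 9 × 0.05 = 1.45; standard error √(2 × 1.45/100) = 0.170. For 0.5 SD, power is 79.3% (t, 18 df). This reproduces the stated 80%.
- m = 3: design effect 1.10; standard error √(2 × 1.10/30) = 0.271. For 1 SD, power is 93.7% (t, 18 df) against the stated 90%. The stated figure is on the cautious side, and this point does not depend on it.

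**2. Ceiling on what the factors can explain.** Cluster-mean variance is ICC + (1 − ICC)/m. Cluster-level factors can explain at most the ICC part.
- m = 10: 0.05/(0.05 + 0.095) = 0.05/0.145 = 34%.
- m = 3: 0.05/(0.05 + 0.317) = 0.05/0.367 = 14%.

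**3. Expected direction.** With exact balance and explained share R², the true standard error is √(1 − R²) times the one reported without the factors: 0.95 at 10% and 0.81 at 34%. The reported error is too large, so alpha falls below 5%.

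**4. Simulation.** There were 22 units, three practice types (assumed 25/50/25%) and two panel sizes (assumed 50/50%), allocated by minimization with a biased coin of 0.8. Cluster-mean variance was 0.145, the explained share was split equally between the two factors, and unit means were analysed by linear regression. The baseline response was not in the model. There were 6,000 runs for alpha and 4,000 for power at 0.5 SD. The difference-triggered rule was read as a baseline chi-square test with p < 0.05.

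| Share explained | Alpha, rule | Alpha, always adjusted | Power, rule | Power, always adjusted | Power lost by the rule |
|---|---|---|---|---|---|
| 0% | 5.23% | 5.05% | 83.3% | 80.6% | −2.7 points |
| 10% | 4.08% | 4.88% | 83.7% | 84.2% | 0.5 |
| 20% | 3.52% | 5.10% | 84.4% | 87.9% | 3.5 |
| 34% | 2.45% | 4.90% | 85.0% | 92.9% | 7.9 |

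The rule flagged either factor in about 0.1% of trials, so its results are those of never adjusting.

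**5. Sensitivity to the allocation algorithm.**
- Deterministic minimization: the factors were never flagged. At shares of 10%, 20% and 34%, alpha was 3.8%, 2.6% and 2.1%, and power was 84.0%, 85.6% and 87.0% against 86.0%, 89.4% and 94.3% adjusted.
- Practice type exactly balanced: alpha was 3.8%, 2.9% and 1.6%, and power was 84%, 85% and 87% against 86%, 90% and 95%.

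**6. Small clusters.** With m = 3, a 1 SD difference and type explaining 10%, 30% or 50% of the between-cluster variance, alpha was 4.8%, 4.6% and 4.3%. Power was 95.8%, 96.0% and 96.2% against 95.7%, 96.2% and 96.7% adjusted. The effect is close to nil.

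**7. Characteristics not balanced by design.** With independent tests at 5%, chance alone flags at least one of 4 in 1 − 0.95⁴ = 18.5% of trials, and at least one of 8 in 1 − 0.95⁸ = 33.7%. The numbers of characteristics are illustrative.

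**The case against.** The strongest reply is that the primary outcome is already adjusted for its baseline response, a prespecified and probably prognostic covariate. That stands. It may recover part of the loss, and the figures above leave it out, so they are an upper guide for the survey scales that have a baseline. It does not help burnout.

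Other limits also stand. The article gives no threshold for a difference and does not say in words that the tests decide; the link is inferred from their place in the same section. But any rule triggered by imbalance still passes over factors that were balanced. Balance was sought across randomized units, whereas the teams now stand at 13 and 16 after withdrawals, so some team-level imbalance is possible and the 0.1% holds for units. Leaving model terms unnamed would ordinarily be a matter for an analysis plan that is not shown; the target here is the conditional rule that the article does state.

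A reader might infer more than the article supports:
- That no covariate enters without a baseline difference. The baseline response does.
- That false positives are inflated. The error runs the other way.
- That the factors could explain half the variance of cluster means. An ICC of 0.05 does not allow it.
- That the baseline tests are at fault for lacking power to find a true imbalance. Under randomization, imbalance is a feature of the sample, and there is no true difference between arms to detect.
- That covariates would be chosen on outcome data. The rule uses baseline characteristics only and can be settled before any 6-month response is examined.

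**Conclusion.** The point holds in a limited form. The stated rule almost never brings practice type and panel size into the model. If they are prognostic, the arm test is conservative. Over an assumed 10% to 34% of cluster-mean variance, true alpha is about 4% down to 2%, and the power lost for 0.5 SD is about 1 to 8 points. The upper end needs the two factors to account for all between-cluster variance at 10 members per cluster. With 3 members, or with weakly prognostic factors, the loss is near nil.

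These figures rest on the protocol's ICC, 22 units of equal size, a cluster-mean analysis standing in for the hierarchical model, and no baseline response in the model. The direction is certain if the factors matter; the size is not known from the article. This is a cheap improvement, not a threat to the validity of a positive result.

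**What to change.** Replace the conditional sentence with a fixed rule. Every arm comparison (survey scales, burnout, patient satisfaction, quality metrics) includes arm, practice type (3 levels), panel size (large or other) and the baseline value of the outcome where one is collected, whatever the baseline comparison shows. Keep the baseline table descriptive and do not select covariates by baseline tests. Label any further adjustment as a sensitivity analysis.

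The change is to wording only and needs no new data. The two factors use 2 + 1 = 3 degrees of freedom out of about 20. If they turn out not to be prognostic, this costs up to about 3 points of power (83.3% to 80.6% in the simulation above).

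### The stated comparison of quality percentages names no baseline term, although six months of pre-study quality data are collected at the same care-team level

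*Protocol article*

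**What the plan says.** Under Methods for data collection, the source of the quality metrics is described thus: "the data were from aggregated medical records for all patients assigned to the care team". The window is wide: "The time frame for collection was from 6 months prior to the start of the study to 12 months post". The Outcomes section gives the frequency and level: "Quality metrics at the care team level are assessed monthly for diabetes, depression, asthma, hypertension, and vascular issues". Each team should therefore have about six pre-study values for each metric, in the same form as the outcome.

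The Statistical methods section sets out two routes. For staff surveys: "For measures collected from the team members, the outcome of interest will be the 6-month post-baseline responses, adjusting for baseline responses". For care-team-level outcomes, it says that "the percentage of patients who met the quality criteria will be compared between arms", with no adjustment for clustering, because individual-level data are not available. That paragraph names no baseline term. A further sentence in the survey paragraph is conditional: "If there are differences in baseline characteristics between the two study groups, these will be accounted for", by means of hierarchical regression models.

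Patient satisfaction shares the second route. The Outcomes section says that a random sample of each team's patients was "surveyed by Press Ganey® every quarter and reported at the site, care team, and provider levels". The six-month pre-study window is stated for the quality metrics only.

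**The concern.** A team's past percentage on a quality metric is likely to predict its later percentage, because assigned patients, staff and local practice persist. With 11 randomised units per arm (Trial status), chance differences in prior performance can be sizeable, and a comparison of follow-up percentages alone carries that variation into its standard error. The pre-study values that could remove part of it are already collected, at the level at which the outcome is analysed, yet the stated comparison gives them no role.

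Quality of care is one of the trial's stated secondary outcomes. Few units make precision scarce, so an avoidable loss matters even for a secondary question.

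**Working it through.** **Figures in the plan.** The article gives no power, precision, team-level standard deviation or pre/post correlation for the quality percentages. Its only power figures, under Sample size, concern individual participants within clusters. For 10 clusters per arm of 10 people with intra-cluster correlation 0.05, the effective number per arm is 100 / (1 + 9 × 0.05) = 69.0. Power for half a standard deviation is then 79.3% by a t test on 18 degrees of freedom, which agrees with the stated 80%. With three per cluster, power for one standard deviation is 93.7%, above the stated 90%. Neither figure bears on the quality percentages.

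**Inputs.** Units: 11 v 11 (Trial status). Two-sided alpha 0.05 (Sample size). Pre/post correlation r of a unit's percentage: assumed, 0.5 to 0.9.

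**Formulas.** In large samples, analysis of covariance multiplies the variance of the arm difference by 1 − r², and the interval width by √(1 − r²). With 22 units, one estimated covariate adds a variance factor of about 19/18, and the t quantile moves from 2.086 (20 df) to 2.093 (19 df). If type (2 df) and panel size (1 df) are also fitted, 16 df remain and the quantile is 2.120. Taking those two factors as balanced by the allocation and as explaining nothing themselves (the least favourable case for including them), the extra variance factor is about 16/15.

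| r (assumed) | Variance factor 1 − r² | Width, large sample | Width, baseline only (19 df) | Width, baseline + type + panel (16 df) |
|---|---|---|---|---|
| 0.3 | 0.91 | 95% | 98% | 100% |
| 0.5 | 0.75 | 87% | 89% | 91% |
| 0.7 | 0.51 | 71% | 74% | 75% |
| 0.8 | 0.36 | 60% | 62% | 63% |
| 0.9 | 0.19 | 44% | 45% | 46% |

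Widths are percentages of the unadjusted interval on 20 df. Example at r = 0.5 with baseline only: √(0.75 × 19/18) × 2.093/2.086 = 0.89.

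**Detectable difference.** By normal approximation at 80% power it is (1.960 + 0.842) × √(2/11) × √(1 − r²) between-unit standard deviations: 1.19 unadjusted, 1.03 at r = 0.5, 0.85 at r = 0.7 and 0.52 at r = 0.9.

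**Thresholds.** Removing more than half the variance needs r² > 0.5, so r > 0.71. Halving the standard error needs r² > 0.75, so r > 0.87. After the small-sample cost, adjustment breaks even near r = 0.24 with the baseline alone and near r = 0.30 with all 4 df.

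**Joint modelling of pre and post.** If the arms' baseline means are left free, an arm-by-period term estimates a difference in changes. For equal pre and post variances its variance factor is 2(1 − r): 1.4 at r = 0.3, 1.0 at r = 0.5, 0.6 at r = 0.7 and 0.2 at r = 0.9. At r = 0.5 that gains nothing, and below 0.5 it is worse than no adjustment. It is not equivalent to analysis of covariance unless the baseline means are constrained equal.

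**The case against.** The strongest objection is that the article is a condensed account and an analysis plan not shown may list covariates. The text excludes an adjustment for clustering; it does not say that the comparison is unadjusted. Collecting a pre-study window also fits an intended pre/post use. This has some force, and it keeps the point modest. But the article is not silent on method here: it states one for these outcomes and, in the same section, a baseline-adjusted one for the surveys. The reason it offers, the lack of individual data, does not explain the difference, because a team-level covariate needs none.

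A second objection is that the conditional sentence on baseline differences covers these outcomes. It works through hierarchical models, which the team-level paragraph does not use. Even if it applied, adjustment would hang on whether a difference is seen, whereas a prognostic baseline improves precision either way.

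Third, the Allocation section says that the groups were balanced on type and panel size. That stands. Prior quality performance was not a balancing factor, but the relevant r is the correlation remaining within type and panel size, so a crude r would overstate the gain.

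Three stronger readings are tempting and unsupported. A reader might infer that most of the available precision is thrown away; that needs r above about 0.71, and no section gives r. A reader might infer that the result would be biased; under randomisation, chance baseline differences are part of the error of a valid unadjusted test, so omitting the covariate costs efficiency only. A reader might infer that the same pre-study data exist for satisfaction; the article describes routine quarterly surveys but does not say that earlier quarters were obtained, and sampling of patients would tend to lower r there.

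**Conclusion.** The point holds as a loss of efficiency in secondary outcomes that can be avoided at almost no cost. Its size depends wholly on an assumed r. At 0.5 the interval would narrow by about a tenth, at 0.7 by about a quarter and at 0.9 by more than half, after the small-sample cost with 22 units; near r = 0.3 the gain vanishes. A fairly high r is plausible for repeated percentages on all patients assigned to the same team, but that is a judgement and not a figure in the article. The calculation also assumes a linear pre/post relation and units of equal weight.

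**What to change.** State that each follow-up quality percentage will be analysed by randomised unit, using analysis of covariance with the unit's mean percentage over the six pre-study months as a prespecified covariate, whether or not the arms differ at baseline. Include the allocation factors type and panel size. Compute the pre-study and follow-up percentages for a unit in the same way where it contains more than one care team. If pre-study and follow-up data are modelled jointly, constrain the baseline means to be equal across arms.

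Do the same for satisfaction if the earlier routine quarterly reports can be obtained; otherwise say that no baseline is available.

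The cost is a few lines of analysis-plan wording, no new quality data, and about 4 degrees of freedom (baseline 1, type 2, panel size 1), leaving 16 of the 20 available to a two-arm comparison of 22 units. The article describes data collection as still ongoing, so at that stage the choice could still be fixed before the results were seen.
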